#### Normal control group

Of the recruited healthy subjects, those with an average weakest link score minus 1 standard deviation will compose the group of individuals without cognitive vulnerability to depression, i.e., the normal control group. Individuals in the normal control group will be interviewed by two experienced psychiatrists using the SCID to exclude those suffering from depression and other axis I diseases. Ultimately, the control group will comprise 30 subjects, and the control group and the intervention and waiting subgroups of the group of individuals cognitively vulnerable to depression will be homogenous in terms of demographic variables and depression symptoms.

The inclusion criteria are described as follows: participants (a) with average CSQ weakest link score minus 1 standard deviation; (b) with Han ethnicity; (c) aged 18–25 years; (d) who are right-handed; (e) who have normal or corrected vision; (f) who are local community residents; (g) who can understand the content of the study, are willing to participate, and are committed to completing the entire experiment; and (h) who signed an informed consent form.

The exclusion criteria are described as follows: participants (a) who meet the diagnostic criteria for depression or other axis diseases; (b) history of taking any antidepressants or antipsychotics; (c) history of alcohol or drug abuse or dependence; (d) history of central nervous system diseases, e.g., head injury or epilepsy; (e) history of multiple sclerosis or major physical diseases; (f) history of electroshock therapy; (g) history of mental illness in first-degree relatives; and (h) contraindications to MRI.

Sample size calculation: An *a priori* power analysis found that a sample size of 75 participants per group (*N* = 150) would be sufficient with a medium effect size (Cohen’s d = 0.0.39) and 65% power (computed with G*power 3.1). These estimates were based on previous research examining changes in HRSD/BDI-II scores before and after CR training when compared to the waiting-list control condition (Berking et al., 2019). Since the sample size projection considered an anticipated 20% dropout rate, the target sample size was 188 patients.

Randomization to treatment will be completed with a computer-generated list of random numbers, and each participant will be randomly assigned to either the intervention group or the control group with a 1:1 allocation and double-blinded. The randomization will minimize group differences in demographic factors and instrument scores (Pocock and Simon, 1975).

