On the other hand, the frequent user of CR showed stronger downregulation of amygdala activation to negative emotion stimuli (Kanske et al., 2012), and CR in healthy individuals can attenuate the excitatory connectivity from the dlPFC to the inferior frontal gyrus (IFG) and increase the inhibitory connectivity from the IFG to the dlPFC, which supports the selection of appropriate alternative CR strategies (reinterpretations) in the IFG, and afterward, inhibition of original interpretations maintained and monitored in the dlPFC (Morawetz et al., 2016). Neurofeedback-guided CR training targeting the left vlPFC improved the frequency of CR strategy use (indexed with ERQ) as well as depression symptoms (Keller et al., 2021). Therefore, CR training may enhance CR ability by changing the functional activity/connectivity pattern of prefrontal-amygdala circuits, which then alleviates cognitive biases and thus depressive symptoms.

Researchers suggested that specific measures using lab-based tasks may be more sensitive to detect training effects (Cohen and Ochsner, 2018). Therefore, in this study, we will combine the RIT, CR training, and fMRI, as well as self-report measures (cognitive/emotion/symptoms) to address the following aims: (1) to examine whether the CR ability (reappraisal inventiveness) of the population with cognitive vulnerability to depression is abnormal; (2) to test the hypothesis that CR training alleviates depressive symptoms through the mediators of cognitive bias (e.g., interpretation bias and/or rumination bias); (3) to investigate the neural substrates (structural/functional) of prefrontal–amygdala circuits through which CR training improves the ability to generate a CR strategy; and (4) to examine the short- and/or long-term effects of CR training on reducing depression symptoms in cognitively vulnerable individuals immediately after intervention and/or 6 months to provide theoretical and practical evidence for early intervention in these populations. We postulate that CR training improves CR ability (RIT) by changing the brain activity/function connectivity of the prefrontal-amygdala circuits, thereby reducing negative cognitive biases (NCPBQ-NIB, NCPBQ-NRB, and CSQ) and improving depression symptoms (CESD) (Figure 1).

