## Methods

Using RIT and CR training in combination with fMRI, we will explore (1) the deficits in CR ability (indexed with RIT) for the depression-vulnerable group; (2) the short- and long-term antidepressant effects of CR training on depression-vulnerable populations; (3) whether it is feasible to reduce negative cognitive biases (negative interpretation bias and/or negative rumination bias) and depressive symptoms of depression by improving reappraisal inventiveness; and (4) the changes in the prefrontal–amygdala circuit induced by CR training, including changes in the functional activation and connectivity of the regions of interest (prefrontal cortex and amygdala) before and shortly after CR training and changes in the volumes of these regions of interest (prefrontal cortex and amygdala) long after CR training (6 months later) (Figure 2).

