### Procedure

#### The effects of cognitive reappraisal inventiveness on individuals cognitively vulnerable to depression

Individuals cognitively vulnerable to depression will be screened using the Cognitive Style Questionnaire (CSQ) developed based on the hopelessness theory and the weakest link method. The weakest link method (Abela and Sarin, 2002) will be used to screen individuals with cognitive vulnerability to depression; it showed the value in predicting changes in depression (Reilly et al., 2012). By using a group of individuals cognitively vulnerable to depression and a normal control group as research participants, we will determine, using the RIT, whether individuals cognitively vulnerable to depression have defects in CR inventiveness before training.

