#### Group of individuals cognitively vulnerable to depression

Of the recruited healthy subjects, those with an average weakest link score plus 1 standard deviation will be assigned to the group of individuals cognitively vulnerable to depression, and whether they have affective disorders and other axis I diseases will be determined by two experienced psychiatrists using the Structured Clinical Interview for DSM Disorders (SCID).

The inclusion criteria are as follows: participants (a) with average CSQ weakest link score plus 1 standard deviation; (b) with Han ethnicity; (c) aged 18–25 years; (d) who are right-handed; (e) with normal or corrected vision; (f) who are local community residents; (g) who can understand the content of the study, are willing to participate, and are committed to completing the entire experiment; (h) have signed informed consent form.

The weakest link composite score of CSQ will be calculated as follows: (1) calculating the scores for the 3 subscales (causes, consequences, and self-worth) of CSQ; (2) standardizing the scores for the 3 subscales and converting them to standard scores, based on which the standard scores for the 3 subscales for each individual are then ranked, in which the highest of the 3 subscale scores represents the final score for each individual’s weakest link; and (3) calculating the average weakest link scores for all individuals. The score is further used to screen individuals in the cognitively vulnerable to depression group (mean score plus 1 standard derivation) or those in the not cognitively vulnerable to depression group (the mean score minus 1 standard derivation).

The exclusion criteria are as follows: participants (a) who meet the diagnostic criteria for depression or other axis diseases; (b) with a history of taking any antidepressants or antipsychotics; (c) with a history of alcohol or drug abuse or dependence; (d) with a history of central nervous system diseases, e.g., head injury or epilepsy; (f) with a history of multiple sclerosis or major physical diseases; (g) with a history of electroshock therapy; (h) with a history of mental illness in first-degree relatives; and (i) with contraindications to MRI.

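### Aim 1's 'normal' controls are the low tail of the vulnerability score, so the baseline RIT contrast can show an association with vulnerability but not an abnormality or deficit

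*Protocol article*

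**What the plan says.** Both groups come from one screened pool of healthy recruits and are cut on one score, the Cognitive Style Questionnaire (CSQ) weakest-link composite. For that composite, "the highest of the 3 subscale scores represents the final score" (Group of individuals cognitively vulnerable to depression).

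- **High group:** "those with an average weakest link score plus 1 standard deviation will be assigned to the group of individuals cognitively vulnerable to depression".
- **Low group:** the same section describes "those in the not cognitively vulnerable to depression group (the mean score minus 1 standard derivation". The section on the normal controls repeats this cut: "those with an average weakest link score minus 1 standard deviation will compose the group of individuals without cognitive vulnerability to depression, i.e., the normal". It thereby equates the low tail with normality, lists the cut as inclusion criterion (a) and fixes the size at 30.

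Aim 1 uses these two groups. The Introduction sets out "to examine whether the CR ability (reappraisal inventiveness) of the population with cognitive vulnerability to depression is abnormal". The opening of Methods speaks of "the deficits in CR ability (indexed with RIT) for the depression-vulnerable group". The first Procedure subsection names the comparison, vulnerable versus normal control on the RIT, and the question as "whether individuals cognitively vulnerable to depression have defects in CR inventiveness before training". The Abstract also words the aim in terms of abnormal ability.

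For aim 1 the article describes no mid-range or unselected group, no RIT norm and no analysis of the score as a continuous variable. The Limitations section does not mention the selection of extremes.

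**The concern.** To say that a group is abnormal or has a deficit, one needs a reference for normal ability. The comparator here is the opposite extreme of the score that defines the vulnerable group. If the two tails differ on RIT, at least two explanations fit equally well: vulnerable people do worse than typical people, or people with unusually low vulnerability do better than typical people. The second is plausible on the article's own account, because the Abstract and Introduction treat reappraisal as a protective factor. The design cannot separate the two, yet the wording of aim 1 reads any shortfall as a fault in the vulnerable group.

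What is at stake is the first listed aim: what it may conclude, and how large the reported gap looks.

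**Working it through.** **The plan's own figure.** No sample size or power is given for aim 1. The stated calculation (75 per group, d printed as 0.0.39 and read as 0.39, 65% power, 188 after 20% dropout) is for training versus waiting list. It reproduces: noncentral t power at two-sided 5% (alpha assumed) is 66.0%, and 150 / 0.8 = 187.5, rounded up to 188. It plays no part below.

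**Inputs.** From the Subjects section: cuts at mean ± 1 SD, and a score that is the highest of three standardised subscales. Assumed: each cut means at or beyond the stated point (the article gives no inequality sign), the score is roughly bell-shaped, and the shares refer to the screened pool before exclusions.

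**Share in each group.** Low tail: Φ(−1) = 0.159. High tail: the same. In neither: 1 − 2 × 0.159 = 0.68. Simulating the highest of three equally correlated normal subscales, with correlations from 0 to 0.9, gives a low tail of 15.7% to 15.9%. The figure of about 16% therefore does not need an exactly normal composite.

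**Distance between the groups.** The mean beyond 1 SD is φ(1)/Φ(−1) = 0.2420 / 0.1587 = 1.525 SD. The tails are 2 × 1.525 = 3.05 SD apart.

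**Distance from typical people.**
- Typical = within 1 SD of the mean: their mean is 0, so the distance is 1.525 and the ratio is 3.05 / 1.525 = 2.0.
- Typical = everyone below +1 SD: their mean is −φ(1)/Φ(1) = −0.2420 / 0.8413 = −0.288, so the distance is 1.525 + 0.288 = 1.813 and the ratio is 3.05 / 1.813 = 1.68.

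With the simulated three-subscale composite, the ratios are 1.90 to 2.00 and 1.63 to 1.68 respectively.

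**Effect on RIT if the relation is linear.** The mean gap is r times the distance on the score, divided by the within-group SD. The article gives no r, so the values below are assumptions (simulated, subscale correlation 0.5):

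| Assumed r (absolute) | d, planned high v low | d, high v within 1 SD | d, high v all below +1 SD |
|---|---|---|---|
| 0.1 | 0.31 | 0.15 | 0.18 |
| 0.2 | 0.62 | 0.31 | 0.37 |
| 0.3 | 0.95 | 0.48 | 0.57 |

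**If the relation is not linear.** Suppose only the low tail differs, by an assumed 0.5 SD in its favour. The planned contrast is then about 0.5 SD, while vulnerable people do not differ from mid-range people. The two-tail data alone cannot tell this case from a true deficit of 0.5 SD.

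**The case against.** Several points on the other side stand.

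- The cut is stated openly, and selecting extremes is a recognised design with a power benefit. The contrast is a valid test of association between vulnerability and RIT. The fault lies in the label and the inference.
- Aim 1 is posed as a question, and the article gives no test or decision rule for it. Under a linear relation vulnerable people really are worse than typical people, so the direction would be right and only the size overstated.
- Groups are to be homogeneous in depression symptoms. Because the Introduction links reappraisal generation to such symptoms, this could shrink the RIT gap. It does not bring the controls' vulnerability scores back to mid-range.

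A reader might infer three stronger things that the documents do not support.

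1. *That the plan would declare a false deficit at a known, high rate.* If only the low tail were better by 0.3 to 0.5 SD, a t-test of 150 versus 30 would be significant in 32% to 70% of trials; at 0.1 to 0.2 SD the figure is 8% to 17%. Both the effects and the test are assumptions from outside the article.
2. *That the error undermines the intervention or the trial's main result.* Training goes ahead whatever the baseline RIT shows, its rationale is argued from earlier literature, and the randomised comparison does not use these controls.
3. *That the controls must be replaced by mid-range people.* That would roughly halve the expected aim 1 difference with only 30 controls, and would also change the third group in the group-by-time model.

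The objection that this is only terminology does not stand. The wording determines the conclusion, and nothing in the article supplies the missing reference for normal.

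**Conclusion.** The concern holds as a limit on what aim 1 may conclude. The planned baseline contrast compares high with low vulnerability; it can support an association with RIT but not an abnormality, defect or deficit relative to typical people. That conclusion follows from the selection rule alone and needs no assumed effect size.

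The size of the overstatement does rest on assumptions. With a roughly bell-shaped score and a linear relation, it is about 1.6 to 2.0 times, the lower end if typical means everyone below +1 SD and the upper end if it means within 1 SD of the mean. A strongly skewed score would move both the 16% share and these ratios. The comparison of training with waiting list is not biased by this choice.

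**What to change.** 1. In both group definitions under Subjects, and in the NC label under Intervention effect analysis, rename the group of 30 the low-vulnerability comparison group.
2. In the Abstract, the aims at the end of the Introduction, the opening of Methods and the first Procedure subsection, restate aim 1 as a high- versus low-vulnerability difference in RIT.
3. Add one sentence saying that this contrast alone will not be interpreted as an abnormality or deficit in vulnerable people.

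The cost is a more modest aim 1 claim. Recruitment, scans, group sizes and models stay as they are. The Ethics statement says that nobody had been recruited at submission, so as of the article the change could precede any data. Drawing controls from the middle of the score range is a trade-off for the investigators and is not required.

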#### Neural mechanism of improvements in cognitive reappraisal inventiveness in individuals cognitively vulnerable to depression through cognitive reappraisal training

Using the group of individuals cognitively vulnerable to depression (divided into intervention and waiting subgroups) and the normal control group as research participants, we will conduct a 4-week (2 sessions/week) CR training program for the intervention subgroup, and before and after training, the intervention and waiting-list control subgroups will undergo fMRI to examine whether CR training can improve reappraisal inventiveness and depression symptoms by regulating the function of the prefrontal–amygdala circuit.

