#### Center for epidemiologic studies depression scale

The center for epidemiologic studies depression scale (CESD) will be used by subjects to self-evaluate their current depressive symptoms (within a week), focusing on depressive emotions or mood rather than somatic symptoms. Subjects with depressive symptoms will undergo preliminary screening to facilitate further diagnosis. The scale contains 20 items in 4 dimensions (negative emotions, positive emotions, physical symptoms, and interpersonal relationships) that are scored on a 4-level scale (“no or rarely, less than once a day,” “sometimes or only a small part of the time in 1 day,” “frequently or half of the time in 1 day,” and “most of the time or all the time in 1 day”); the higher the score is, the more severe the level of depression.

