#### Reappraisal ability/tendency

##### Reappraisal inventiveness test

RIT includes 4 scenes that can trigger emotions. Participants are asked to imagine themselves in the scene as vividly as possible within a specified time (3 min), after which they are asked to think of reappraisals that can change the induced emotion within 20 s and then record the reappraisals in 3 min. RIT was scored on two scales: (a) RIT-fluency was indicated by the number of reappraisals generated and (b) RIT-flexibility was indicated by the number of categories of different reappraisals (Weber et al., 2013). To improve the internal validity of the test, we set the induced emotions to sad and happy. Before the test, the subjects will be given examples to illustrate how to generate as many reappraisals as possible for a given emotional stimulus so that they can transfer to the formal test.

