### Statistical analysis

#### Behavioral and self-report data

##### Intervention effect analysis

A 3 (group: CR = cognitively vulnerable intervention subgroup; WC = cognitively vulnerable waiting-list control subgroup; NC = normal control group) × 3 (time point: T_0_ = pretraining, T_1_ = post-training, T_2_ = 6-month follow-up) mixed design will be adopted. Using the HLM analysis, as well as mediating/modulating effect analyses, we will investigate (1) hypothesis 1, whether the changes in negative cognitive biases and depressive symptoms across time 1 and time 2 differ significantly among groups and (2) hypothesis 2, whether the changes in negative cognitive bias (negative interpretation bias and/or negative rumination bias) pre- and post-training could predict depression symptoms at T_1_ and/or T_2_.

To test hypothesis 1, we will conduct an HLM analysis with time (0 = pretraining; 1 = post-training), group (0 = CR; 1 = WC; 2 = NC), and the interaction between time and group as predictor variables and the with CESD score as the outcome variable. To test hypothesis 2, we will conduct mediating/modulating effect analyses among CR ability (RIT) and tendency (ERQ), negative cognitive bias (NCPBQ), cognitive vulnerability (CSQ), and depressive symptoms (CESD) at T_1_ and/or T_2_. The HLM and mediating/modulating effect analyses will be conducted in SPSS (Statistical Product and Service Solutions) software version 22.0 (SPSS, Inc., Chicago, IL, United States) combined with the PROCESS Macro (Hayes, 2012).

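### The randomised comparison is called double-blinded, but a waiting-list comparator and self-rated outcomes mean that participants and the training experimenter cannot be blinded

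*Protocol article*

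**What the plan says.** The randomisation paragraph, which follows the sample-size paragraph under 'Normal control group', states that "each participant will be randomly assigned to either the intervention group or the control group with a 1:1 allocation and double-blinded". It does not say who is blinded or how.

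Other sections describe the two arms and the outcome:

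- **Intervention arm.** Under 'Neural mechanism of improvements in cognitive reappraisal inventiveness…': "we will conduct a 4-week (2 sessions/week) CR training program for the intervention subgroup". 'Training procedure' gives eight sessions of 180 trials each. An experimenter checks that instructions were followed and records what participants report after each block.
- **Comparator.** The same 'Neural mechanism' section says that "the intervention and waiting-list control subgroups will undergo fMRI", and 'Intervention effect analysis' defines "WC = cognitively vulnerable waiting-list control subgroup". No sham or attention-control training is described.
- **Primary outcome.** CESD "will be used by subjects to self-evaluate their current depressive symptoms", and the model for hypothesis 1 takes the "CESD score as the outcome variable".
- **Other measures.** NCPBQ, CSQ and ERQ are participant-completed questionnaires. The RIT yields free answers that are then scored: "RIT-flexibility was indicated by the number of categories of different reappraisals".

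The 'Limitations' section does not mention the absence of blinding.

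**The concern.** Double-blinding is one of the first things a reader uses to judge risk of bias. Here the term is attached to a design that cannot deliver it. A participant who attends eight training sessions knows it, and so does one who waits. For a self-rating the participant is also the outcome assessor, so no arrangement among data handlers can protect CESD.

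The same exposure reaches the mediation analysis. The proposed mediators (the interpretation and rumination subscales of NCPBQ) and the outcome (CESD) are reported by the same unblinded people. If knowing the arm shifts both, the shift could look like the pathway the trial hopes to show. A reader told that the trial is double-blind would discount this possibility.

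**Working it through.** **1. Which comparison the term refers to.** The normal control group is selected by a low CSQ weakest-link score, so it is not randomised. The vulnerable group is divided into intervention and waiting subgroups. The control group in the randomisation sentence can therefore only be the waiting list.

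**2. Who could be blinded.**

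| Role | Source in the article | Can blinding hold? |
|---|---|---|
| Participant | Training for one arm, waiting for the other, no sham | No |
| Experimenter at the sessions | 'Training procedure': checks compliance with the training | No |
| Assessor of CESD, NCPBQ, CSQ, ERQ | The participant | No |
| Psychiatrists giving the SCID | 'Primary outcome' and 'Subjects': used at recruitment | Not an assessor after randomisation |
| RIT scorer | 'Reappraisal inventiveness test' | Possible; not described |
| Imaging analyst | 'Data analysis' (neuroimaging) | Possible; not described |

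The SCID appears under the primary-outcome heading, but its stated use is diagnosis and screening when subjects are recruited. It does not supply a blinded endpoint.

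**3. The plan's own sample-size figures (context only).** Inputs from 'Sample size calculation': 75 per group, an effect printed as 0.0.39 and read here as 0.39, 65% power, 20% dropout. No alpha is stated; two-sided 0.05 is assumed.

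- Standard error of the standardised difference: √(2/75) = 0.1633.
- Power: Φ(0.39/0.1633 − 1.960) = Φ(0.428) = 66.6% by normal approximation; 66.0% by t-test. Stated: 65%.
- n per group for 65% power: 2(1.960 + 0.385)²/0.39² = 72.3, rounded up to 73; by t-test 73.3, rounded up to 74. Stated: 75.
- Dropout: 150/(1 − 0.20) = 187.5, rounded up to 188, as stated.

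The figures reproduce closely. The blinding point does not depend on them.

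**4. Illustration of what is at stake.** Assume no true effect, 75 per arm, two-sided alpha 0.05, a simple two-arm comparison, and a reporting bias of b SD from knowing the arm. Then

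rejection rate = 1 − Φ(1.960 − b/0.1633) + Φ(−1.960 − b/0.1633).

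- b = 0.10: b/0.1633 = 0.612, giving 1 − Φ(1.348) + Φ(−2.572) = 9.4% (t-test 9.3%).
- b = 0.20: b/0.1633 = 1.225, giving 1 − Φ(0.735) + Φ(−3.185) = 23.2% (t-test 22.9%).

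The values of b are assumptions, and the planned analysis is a hierarchical model over three groups rather than this test. The rates show sensitivity; they do not estimate the bias in this trial.

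**The case against.** Several points can fairly be made on the other side.

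- *A condensed article may leave the list of blinded roles to the full protocol.* This stands for the missing list, which is not the finding. The finding is an affirmative statement that the described design contradicts, and no fuller document can blind a participant on a waiting list.
- *The term may have meant allocation concealment, or blinded scorers and analysts.* That is possible. If so, the wording is wrong, and neither arrangement would protect CESD.
- *The waiting list and the self-rating are openly described, and a waiting list is a legitimate comparator.* This stands. No new arm or endpoint is asked for, and a careful reader could see the limitation. The label still tells that reader the opposite.
- *The rejection rates rest on an assumed bias and would be the same whether or not the term is printed.* This stands, so they are illustration only.

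A reader might infer three stronger things that the documents do not support:

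- *That a known share of the planned effect is expectancy.* The article gives no size for such a bias. Its planning effect also came from a comparison with a waiting list, so any expectancy component could already sit inside 0.39.
- *That every bias favours CR, or that the whole mechanistic claim rests on it.* The direction is plausible but not shown. The mechanism also uses RIT performance, regional activation, connectivity and volumes, which are not self-reports. Only the paths involving questionnaires carry reporting bias of this kind.
- *That a blind-scored RIT would check expectancy in CESD.* It would not. The RIT is not a depression outcome, and coding the sheets does not blind the person who writes the answers.

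**Conclusion.** The point holds as an internal contradiction. For the randomised comparison of CR with the waiting list, neither participants nor the training experimenter can be blinded. The protection implied by the term is absent for CESD and for NCPBQ, CSQ and ERQ. This follows from the article's own description and rests on no outside assumption.

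Its numerical size is unknown. Under the assumptions set out in the working, a reporting bias of 0.10 to 0.20 SD would give a rejection rate of about 9% to 23% instead of 5%. Correcting the wording does not change those rates. What it changes is what readers are told about the primary outcome and how far the conclusions on questionnaire outcomes and mediation can go. The statement should be corrected before the trial is reported.

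**What to change.** 1. Delete the term *double-blinded* from the randomisation paragraph. If allocation concealment was meant, say that instead.
2. State that participants and the experimenter who runs the training are not blinded.
3. Score RIT answers and process images from files coded without arm or time point, with RIT scoring done by someone who did not run the training. Name these as the blinded roles.
4. Add to the Limitations and carry into the conclusions: differences between CR and waiting list in CESD, NCPBQ, CSQ and ERQ, and mediation paths built on them, may include expectancy effects.

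Coding the files removes scorer bias only. Participant expectancy and effort on the RIT remain.

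Cost: wording changes and ID-coding of RIT sheets and image files. The article does not say who scores the RIT; if the training experimenter was to do it, a different scorer is needed. Randomisation, sample size and the planned models are unchanged. The ethics statement says that no one had been recruited at submission, so as of that date the coding could be set up before any data were collected.

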Intervention studies demonstrated that individuals’ CR ability can be improved through training and could predict changes in depressive symptoms. CR training could alleviate depressive symptoms and negative emotions, improve happiness and life satisfaction in patients with depression (Berking et al., 2013; Ehret et al., 2014; Weytens et al., 2014), and decrease short- and long-term negative emotions in healthy individuals (Denny and Ochsner, 2014). Enhancement of self-reported CR frequency after CR training compared to the wait-list control condition (WLC) could reduce the depressive symptom severity of depressed patients (Berking et al., 2019). The change in CR tendency after CBT could predict a decrease in depressive symptoms in patients with depressive disorder (Forkmann et al., 2014). A meta-analysis of emotion regulation intervention in clinical populations showed improvement in emotion regulation (including CR) tendencies (Moore et al., 2022). However, studies of the antidepressant effect of CR training on cognitively vulnerable individuals with depression are still lacking. Yuan et al. (2014) proposed that the use of CR training could reduce the vulnerability of adolescents to negative emotions, whose development stage is prone to emotional disturbances. Thus, empirical evidence for the training effects of CR on cognitively vulnerable individuals is still needed.

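### The primary CESD model uses baseline CESD only as a repeated outcome, so the randomised comparison has change-score precision; baseline adjustment would be more precise, and the allocation text that bears on its standard error needs reconciling

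*Protocol article*

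**What the plan says.** **Model.** The section Intervention effect analysis tests hypothesis 1 with a hierarchical linear model. CESD is the outcome; time (0 = pretraining, 1 = post-training), group (training, waiting list, normal control) and "the interaction between time and group as predictor variables" are listed. No other covariate appears.

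**Allocation.** The paragraph after the sample size calculation says "Randomization to treatment will be completed with a computer-generated list of random numbers", that participants are "randomly assigned to either the intervention group or the control group with a 1:1 allocation", and then "The randomization will minimize group differences in demographic factors and instrument scores". The last sentence cites a minimisation reference. The factors are not named individually.

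**Sample size.** The same part of the article states that "a sample size of 75 participants per group (*N* = 150) would be sufficient" with a "medium effect size (Cohen’s d = 0.0.39) and 65% power". The estimate is based on changes in HRSD/BDI-II against a waiting list in an earlier trial. A 20% dropout allowance gives a target of 188.

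**The concern.** Pretraining CESD is collected on everyone and, in the randomised arms, has the same expected value. A model that treats it as just another outcome row does not use that fact. The time-by-group coefficient is then the difference between arms in mean change, which carries the full noise of two measurements. In a trial planned at 65% power, giving up precision that is already in the data matters.

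The allocation text adds a second question. If allocation actively balances the arms on baseline CESD, an analysis that does not condition on baseline CESD reports a standard error larger than the true one. Whether that applies cannot be settled while a random-number list and a minimisation claim stand side by side.

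**Working it through.** **Inputs.** From the article: 75 per arm, d printed as 0.0.39, 65% power, 20% dropout, and the predictor list. Assumed because not given: two-sided alpha of 0.05, equal CESD variance at T0 and T1, and r for CESD. Retest figures are given for the CSQ (0.59 over eight weeks) and the ERQ (0.82 and 0.79), but not for the CESD. The range r = 0.3 to 0.8 is therefore an assumption.

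**Step 1: the plan's own figures.** With d = 0.39, the noncentrality is 0.39 × √(75/2) = 2.388. Power is 66.0% by the noncentral t and 66.6% by the normal approximation, which agrees with the stated 65%. A one-sided 5% test would give about 77%, and d = 0.039 only about 6%, so two-sided 5% with d = 0.39 is the reading that fits. For dropout, 150/0.80 = 187.5, rounded up to 188. Both figures reproduce.

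**Step 2: variance.** Let the CESD variance be σ². Per participant:
- the change score has variance 2(1−r)σ²;
- follow-up adjusted for baseline has residual variance (1−r²)σ²;
- the ratio, adjusted to change, is (1−r²)/[2(1−r)] = (1+r)/2, which is below 1 for every r below 1.

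**Step 3: power.** The article does not say whether d is divided by the SD of the change or of the raw score. Both readings are shown (noncentral t, 75 per arm).

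If d is on the change SD, the listed model uses 0.39 and the adjusted analysis uses 0.39/√((1+r)/2):

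| r | effective d, adjusted | listed model | baseline-adjusted |
|---|---|---|---|
| 0.3 | 0.484 | 66.0% | 83.7% |
| 0.5 | 0.450 | 66.0% | 78.2% |
| 0.8 | 0.411 | 66.0% | 70.6% |

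If d is on the raw SD, the listed model uses 0.39/√(2(1−r)) and the adjusted analysis uses 0.39/√(1−r²):

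| r | effective d, listed / adjusted | listed model | baseline-adjusted |
|---|---|---|---|
| 0.3 | 0.330 / 0.409 | 51.8% | 70.1% |
| 0.5 | 0.390 / 0.450 | 66.0% | 78.2% |
| 0.8 | 0.617 / 0.650 | 96.3% | 97.7% |

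**Step 4: if allocation fully balances baseline CESD.** The listed model's standard error then exceeds the true one by the factor √(2/(1+r)), and the true type I error is 2[1−Φ(1.96 × factor)].

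| r | SE factor | true two-sided type I error |
|---|---|---|
| 0.3 | 1.24 | 1.5% |
| 0.5 | 1.15 | 2.4% |
| 0.8 | 1.05 | 3.9% |

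In that scenario, with d on the change SD and the normal approximation, the listed model has 67% to 70% power. The adjusted analysis has 84%, 79% and 71% at the three values of r. Partial balance would put the type I error between the tabulated value and 5%.

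**Step 5: other covariates.** A random-intercept model was fitted to simulated data with 75 per arm, with and without a time-invariant covariate as a main effect. The time-by-group estimate (−0.682) and its standard error (0.159) were the same both ways. Such a covariate cancels out of the within-person change. It helps only as a covariate for the follow-up score or through an interaction with time.

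**The case against.** The strongest reply is that the listed model is a legitimate analysis. A reader might infer that baseline is ignored; it is not, because pretraining CESD is the time-0 outcome. A reader might also infer that leaving out demographics widens the interval for the time-by-group effect; Step 5 shows that it does not when they would enter as main effects. Both points stand. What remains is less efficient use of baseline CESD.

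A second stronger reading is that the standard error is definitely too large. The documents do not establish this. It requires real minimisation with baseline CESD among the factors, whereas the text says only that instrument scores are balanced and also describes a random-number list. Minimisation with a random element also needs random numbers, so the two sentences may be compatible, but as written they leave the method unclear. Under a simple list the standard error is valid. Where an error exists, it is conservative.

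Third, a full analysis plan may name covariates, and a condensed article need not list them all. That limits the weight of the point. It does not remove it, because the article states the predictor list rather than staying silent.

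**Conclusion.** The point holds as an improvement to a stated model, not as an error that invalidates the trial. Baseline adjustment reduces the variance of the randomised contrast to (1+r)/2 of its change-score value. That direction holds for any r below 1, under equal variances at the two visits.

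The size rests on r and on the scale of d, neither of which the article gives. The power gain runs from about 18 percentage points at r = 0.3 under either reading (66.0% to 83.7%, or 51.8% to 70.1%) to between 1 and 5 points at r = 0.8. It would be tempting to say that power stays near 65% when 78% is available at no cost. That pair of figures needs an assumed r of 0.5, and on the raw-SD reading the listed model is not fixed near 65% at all.

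The stated 65% and 188 are not wrong. The misprinted d, and its origin in a study of depressed patients measured on other scales, are side points and do not carry this conclusion. The conservative standard error (up to about 15% at r = 0.5, with type I error as low as about 2.4%) is conditional on the allocation method, which the article must first make clear.

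**What to change.** 1. State one allocation method. If it is a random-number list, drop the minimisation claim. If it is minimisation, say so, describe its random element and name the factors.
2. Estimate training minus waiting list on CESD at T1, and at T2, with T0 CESD as a covariate. Alternatively, use a longitudinal model that constrains T0 means to be equal in the two randomised arms only. The normal control group is not randomised and must stay outside that constraint.
3. If minimisation is used, include its factors as covariates for follow-up CESD, or as covariate-by-time terms in the longitudinal model. Main effects alone would leave the time-by-group standard error unchanged.
4. Print d as 0.39, say which SD it is divided by, state alpha and sidedness, and restate power for the adjusted analysis over a range of r.

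The cost is a few lines of wording. No new data, visits or participants are needed. The restated power will be a range rather than one number.
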